### Study outcomes

Primary outcomes: changes from baseline, and after 2 and 6 months, in DSRQ score, urinary sodium values and mean BP as assessed by ABPM.

Secondary outcomes: questionnaire sensitivity and specificity by the comparison of DSRQ scores to urinary sodium values.

### Sample size

Sodium reduction is assessed by urinary sodium values and estimated sodium intake; thus, sample size was calculated according to sodium reduction. The DSRQ was developed in order to improve sodium-restriction adherence [19], the more adherence the less sodium intake, which, in turn, reduces urinary sodium values and mean BP [26]. Sample size was estimated based on the data of the previous study with the same hypertensive population, with an estimated mean of 3900.98 ± 1602.2 mg/day (168.5 mmol) of sodium [27]. We expect to obtain a 100-mmol (2300-mg/day) reduction with the intervention; moreover, in order to detect a 40-mmol urinary sodium difference, a standard deviation of approximately 69.2 mmol, an alpha error of 5% and power of 80%, the study will include 48 participants in each group.

We opted for a 20% increase over the initial number to account for follow-up loss or subject withdrawal so that we arrived at a total of 120 participants included and assigned to either the intervention or the control group.

### Statistical analysis plan

The sample characteristics will be presented by descriptive statistics, and the results will be expressed as mean, standard deviation and percentage. Pearson’s chi-square test and Student’s *t* test will be used to compare categorical and continuous variables, respectively, between groups. In order to analyze educational intervention effectiveness, deltas of sodium urinary excretion will be compared by analysis of covariance.

The questionnaire sensitivity and specificity to identify low-sodium-restriction adherence will be evaluated comparing DSRQ score results to sodium values estimated by urine collection and ROC curve.

All data will be analyzed according to the intention-to-treat principle. The statistics analysis will be carried out in PASW Statistics 18® (International Business Machines Corp., Armonk, NY, USA). A *P* value < 0.05 will be considered statistically significant.

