#### Spot urine analysis

Spot urine will be collected to estimate sodium intake, at baseline, after 2 months and at the end of the follow-up (6 months).

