#### 24-h ambulatory blood pressure monitoring (ABPM)

AMPB will be performed using Spacelabs 90207 devices (Redmond, WA, USA). The protocol includes BP measurements every 15 min during daytime (6:00 a.m. to 10:00 p.m.) and every 20 min during nighttime (10:00 p.m. to 6:00 a.m.). ABPM will be considered satisfactory if at least 16 valid readings during daytime and 8 valid readings during nighttime are obtained [25]. Participants will be evaluated by ABPM at the baseline and at the end of the follow-up (6 months) in order to register BP during both sleep and wakefulness.

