#### Dietary Sodium Restriction Questionnaire (DSRQ)

The participants will answer the DSRQ for the assessment of sodium-restriction adherence at the baseline, 2 months and at the end of the follow-up. This application will guide the educational intervention.

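### Analysis of covariance is planned for urinary sodium only; the DSRQ and ABPM changes are equally primary and should get the same baseline-adjusted model

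*Protocol article*

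**What the plan says.** The Study outcomes section of the protocol article lists the primary outcomes together, without ranking them: "changes from baseline, and after 2 and 6 months, in DSRQ score, urinary sodium values and mean BP as assessed by ABPM".

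The Statistical analysis plan section begins with descriptive statistics for the sample. It then says that Pearson's chi-square and Student's t "test will be used to compare categorical and continuous variables, respectively, between groups", without saying which variables are meant. The next sentence turns to the effectiveness of the intervention and names one outcome: "deltas of sodium urinary excretion will be compared by analysis of covariance". It does not name the covariate. The section gives no effectiveness model for DSRQ or ABPM.

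Baseline is measured for all three outcomes:
- **Urinary sodium:** spot urine at baseline, 2 months and 6 months (Spot urine analysis).
- **ABPM:** baseline and 6 months (24-h ambulatory blood pressure monitoring).
- **DSRQ:** "The participants will answer the DSRQ for the assessment of sodium-restriction adherence at the baseline, 2 months and at the end of the follow-up" (Dietary Sodium Restriction Questionnaire).

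The Sample size section is built on sodium alone, "in order to detect a 40-mmol urinary sodium difference" with "a standard deviation of approximately 69.2 mmol", a 5% alpha and 80% power. It arrives at 48 per group, and at 120 in total after allowing for 20% loss.

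**The concern.** Three outcomes of the same rank are treated unequally. Sodium gets a model that can use the baseline value. DSRQ and ABPM have only the general t test, which cannot. An analyst who follows the text would compare the change in DSRQ and in ABPM between arms without adjustment.

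What is at stake is precision. Change scores subtract the whole baseline value, whereas the best linear use of baseline subtracts only the part that predicts follow-up. When r is below 1, subtracting all of it adds noise. It also over-corrects if the arms happen to differ at baseline. Blood pressure by ABPM is named in the trial's hypothesis, and no sample size was worked out for it or for DSRQ, so precision on these two outcomes should not be given away.

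**Working it through.** **1. The plan's own figure.** Inputs from the Sample size section: difference 40 mmol, SD 69.2 mmol, alpha 5% (taken as two-sided), power 80%.

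- Normal approximation: n = 2 × (1.960 + 0.842)² × (69.2/40)² = 2 × 7.85 × 2.993 ≈ 46.98, so 47 per group.
- Two-sample t test (noncentral t): n = 47.96, so 48 per group, with power 0.800 at 48.
- Loss: 48/0.8 = 60 per arm, 120 in total.

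The stated 48 and 120 reproduce. The calculation is that of an unadjusted two-sample comparison and takes no credit for baseline adjustment.

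**2. Cost of leaving baseline out (DSRQ and ABPM).** Let σ be the SD of an outcome, assumed equal at baseline and follow-up, and r the correlation between the two.

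- Variance of a change score: 2σ²(1 − r)
- Residual variance with baseline as covariate: σ²(1 − r²)
- Ratio: 2(1 − r)/[(1 − r)(1 + r)] = 2/(1 + r)

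The documents give no r, so it is shown as a range. The third column is the square root of the second. The last column is 48 × (1 + r)/2.

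| r (assumed) | Variance, t test on change ÷ ANCOVA | CI width ratio | ANCOVA patients per arm that match 48 under the t test |
|---|---|---|---|
| 0.3 | 1.54 | 1.24 | 31.2 |
| 0.6 | 1.25 | 1.12 | 38.4 |
| 0.8 | 1.11 | 1.05 | 43.2 |

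The ratio does not depend on σ, so it applies to DSRQ and ABPM although the documents give no SD for either. If the SDs at the two times differ (σ₀ at baseline, σ₁ at follow-up), the variance of change minus the ANCOVA variance equals (σ₀ − rσ₁)², which is never negative. Apart from one residual degree of freedom (93 instead of 94 with 48 per arm), adjustment does not lose.

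**3. Chance imbalance.** With 60 per arm, the standard error of the baseline difference is σ × √(2/60) = 0.18σ. Given a baseline difference d, the expected change-score difference is off by −(1 − r)d. For d of one standard error, that is 0.7 × 0.18σ = 0.13σ at r = 0.3 and 0.2 × 0.18σ = 0.04σ at r = 0.8. These errors average to zero over randomisations. Baseline-adjusted ANCOVA removes them in the trial at hand.

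**4. Sodium under the model already planned.** If 69.2 mmol is an SD of levels, the residual SD with baseline in the model is 69.2 × √(1 − r²). Normal approximation:

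| r (assumed) | Residual SD, mmol | n per group for 80% | Power at 48 per group |
|---|---|---|---|
| 0.3 | 66.0 | 43 | 0.84 |
| 0.6 | 55.4 | 31 | 0.94 |
| 0.8 | 41.5 | 17 | 0.997 |

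That 69.2 is an SD of levels is the likely reading: the cited source figure is 1602.2 mg/day around a mean intake, and 1602.2/23 = 69.7 mmol. On that reading the sizing is conservative.

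**The case against.** The strongest reply is that the plan never assigns the t test to DSRQ or ABPM. The sentence on t and chi-square tests directly follows the one on sample characteristics and precedes the separate sentence on effectiveness, so it may concern baseline description only. The article would then be silent on these two models, and a condensed article may leave that to the full plan. The first part stands: the t test reaches these outcomes by default, and no one should report it as their named analysis. The second part does not dispose of the point. The section does state an effectiveness model, and states it for one of three equal primaries. A reader who follows the text has only an unadjusted method for the other two. On either reading the same sentence puts it right.

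Three stronger readings are tempting, and the documents do not support them:

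- **That sodium is underpowered.** A raw comparison of deltas with an SD of levels would have power of about 0.67 at r = 0.3. But the plan states analysis of covariance, which takes a covariate, so that figure describes an analysis it does not propose. It also depends on a low r: at r = 0.7 the same raw comparison has power 0.96.
- **That the unadjusted test is biased.** It is not. In expectation, regression to the mean affects both arms alike under randomisation.
- **That a t test on final values is in play,** with 1/(1 − 0.6²) = 1.56 times the ANCOVA variance at r = 0.6. The primaries are defined as changes, so this comparison does not apply.

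It is also fair to say that analysing deltas by ANCOVA is no error: with baseline as covariate it gives the same treatment effect as modelling the follow-up value.

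**Conclusion.** The point holds as a free improvement. Baseline adjustment is planned for one of three equal primary outcomes, and the general t test is the only stated fallback for the other two. If it is used on change, their variance is 1.54 times (r = 0.3) to 1.11 times (r = 0.8) what the collected data allow, and chance baseline imbalance stays in the estimate. These sizes rest on an assumed r and on equal SDs at the two times; the direction rests on neither. Validity is not in question, and the sample size stands. For sodium, all that is needed is to name baseline as the covariate in the model already chosen.

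**What to change.** Replace the effectiveness sentence in the Statistical analysis plan section with a statement along these lines: each of the three primary outcomes will be analysed by analysis of covariance of the follow-up value (or, equivalently, the change from baseline) on treatment arm and the baseline value of that same outcome, at each follow-up time at which it is measured, and the adjusted difference between arms will be reported with its 95% CI. Add that the t and chi-square tests serve to describe the sample.

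The cost is a sentence or two of text. Baseline is already collected for all three outcomes, analysis of covariance is already in the plan for sodium, and neither the software nor the number of participants has to change.

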## Discussion

This trial evaluates the hypothesis that patients with hypertension, when participating in an educational intervention for sodium restriction, improve their low-sodium diet adherence, thus decreasing blood pressure values and sodium urinary excretion. The educational intervention for sodium restriction will be planned based on the application of the DSRQ in patients with hypertension. The DSRQ was adapted to Brazilian Portuguese [28] and validated for heart failure (HF) [29] to help identifying facilitators and barriers to sodium-restriction adherence, and to be useful in clinical practice to guide the development of educational and counseling interventions to patients [19]. Considering the importance of assessing salt-restriction adherence and the lack of instruments for easy application in the care routine, the DSRQ was validated for hypertension [21] with the purpose of being an instrument to assess low-sodium diet adherence which can contribute to the planning of educational interventions in patients with hypertension.

The DSRQ was developed for patients with HF [19] and applied to evaluate the effectiveness of an educational intervention, based on the TPB. It has been demonstrated that such an intervention was effective to reduce sodium intake compared to the control group after 6 months. It was also found out that the attitude towards a low-sodium diet improved during the 6 weeks of the intervention. Concluding, educational programs that are carefully designed have the potential to produce the desired results, such as low-sodium diet adherence in patients with HF [26].

For any health recommendation to be successful it is necessary to overcome behavioral barriers to dietary change and the influence of interindividual variation in dietary response [30]. However, it is not yet clear what theoretical basis is the best to select intervention methods and strategies; nevertheless, TPB is the theory most used to understand and predict health behaviors, including food-related behaviors [22]. According to TPB, behavior is a function of intention to act and the perception of control over behavior, the intention being determined by three variables: attitudes related to behavior, subjective norm and perceived behavioral control [22].

People with higher perception of their capabilities usually perceive the difficulties as problems to be experienced and not as threats to be avoided; on the other hand, people who are hesitant regarding their own capacities, perceive difficult tasks as threatening, and thus, the more confident that the person is in their ability to follow a healthy and low-sodium diet, the more likely they are to follow this recommendation [14].

### Potential biases

This study has some limitations. It is difficult to target a specific behavior concerning salt intake because salt can originate from several natural sources or be added to food during cooking or food processing. The instrument is self-reported, and self-reported behavior measurements can present a range of bias such as data credibility. The open-label design can introduce some potential for biases and the sample size limits the external validity.

### Trial status

Participant recruitment of this randomized clinical trial begun in November 2015.

## Abbreviations

ABPM: 24-h ambulatory blood pressure monitoring
BMI: Body Mass Index
BP: Blood pressure
DSRQ: Dietary Sodium Restriction Questionnaire
HF: Heart failure
TPB: Theory of Planned Behavior
WC: Waist circumference
